#### Chronic inflammation

Chronic inflammation through (over)stimulation of the immune system, also called inflamm-aging appears to be one of the hallmarks of aging while achieving healthy longevity lies in balancing the pro-inflammatory and anti-inflammatory signals. In order to measure this background inflammation, we will use hs-CRP.

#### 36-item short form survey (SF-36)

The 36-Item Short Form Survey (SF-36) is a commonly used, well-researched, self-reported measure of health. The SF-36 is often used as a measure of a person or population’s quality of life (QOL).

## Participant timeline {13}

### Schedule of assessments

**Table Tabe:** 

Procedures and assessments	Visit 1	Visit 2	Visit 2a	Visit 3	Visit 4
	Screening	Baseline	Phone call	Interim assessment	EOS
	Day -28 to -1	Day 0	Within 6 days of baseline	Day 42±7	Day 91 +7
Informed consent	x				
Review of subject eligibility	x	x			
Demographics^1^	x				
Medical history	x				
Auscultate the heart to check for murmurs	x				
Vital signs^2^	x	x		x	x
ECG	x				
Hematology and biochemistry	x^3^			x^4^	x^3^
DNA methylation (TruDiagnostics)		x			x
SF-36 questionnaire		x			x
Assessment of ability to complete 30-Second Chair-Stand Test	x				
Randomization		x			
Allocation of weekly medication^5^		x		x	
Confirm participant day 1			x		
Weekly participant contact			x^6^		
Adverse event collection		x	x	x	x
Distribute subject diary card		x		x	
Collect subject diary cards				x	x
30-Second Chair-Stand Test		x		x	x
Hand grip strength		x		x	x
6-min walk test		x			x

^1^Race, gender at birth, contact details, height, and weight

^2^Resting heart rate, blood pressure, and oxygen saturation

^3^Full blood count, eGFR, urea and electrolytes, LFTs, HbA1c, lipids, IGF-1, hs-CRP

^4^Full blood count, LFTs, lipids

^5^Allocation of investigational product for 6-week period, followed by a 7-week period

^6^Participants are to be contacted by phone each week. Participants who cannot be reached following two phone contact attempts in a week can be sent a text message or email

### Participant activities schedule

Weeks 1–13 exercise and dosing schedule.

Day 1 Week 1 must begin within 6 days of Day 0 (baseline visit).

**Table Tabf:** 

**Weekly schedule**	**Exercise schedule**	**Dosing schedule**
Day 1	Training program	No treatment
Day 2	Rest day	No treatment
Day 3	Training program	No treatment
Day 4	Rest	No treatment
Day 5	Training program	No treatment
Day 6	Rest day	Placebo/rapamycin in the morning
Day 7	Rest day	No treatment

## Sample size {14}

The sample size was selected primarily to satisfy logistic constraints of this feasibility study. As this study is not confirmatory, we do not predicate the sample size primarily on power considerations: arm sizes of 20, assuming no withdrawals, will provide 80% and 90% power, respectively, to detect fairly large Cohen’s effect sizes of 0.8 and 0.9, respectively, at a nominal significance level of 0.1.

In regard to safety, the arm sizes and post-randomization follow-up time will enable to detect rate ratios of adverse events between the sirolimus (rapamycin) and placebo arms varying between 2.4 and 3.7, dependent upon the rate in the placebo arm and the dispersion of the data. Sample sizes of 12 per arm have been indicated as sufficient for pilot or feasibility studies [34]. However, our feasibility objective of variance estimation makes it preferable to aim for a total sample size of 40, as a 95% confidence interval for the variance will then have expected half-width of less than half the true variance, providing a reasonably precise estimate.

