## Trial design {8}

This study is a randomized, double-blind, placebo-controlled trial designed to evaluate the effects of once-weekly sirolimus (rapamycin) 6 mg on muscle strength and endurance in older adults participating in a thrice-weekly exercise program for 13 weeks. Randomization will be carried out using block randomization with stratification for age with a 1:1 allocation to receive either once-weekly sirolimus (rapamycin) or a placebo in addition to their exercise regimen. The primary, exploratory objective is to evaluate whether this combined intervention is at least equivalent to regular exercise alone in enhancing muscle performance in older adults.

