## Outcomes {12}

### Primary outcome

Our primary outcome is to evaluate the difference in the improvement of muscle performance, as measured by the 30-Second Chair-Stand Test (30CST), following a 13-week exercise regimen combined with weekly dosing of sirolimus (rapamycin) compared to exercise alone.

This assessment is crucial in establishing that the weekly administration of rapamycin, which inhibits the mechanistic target of the rapamycin (mTORC1) pathway, does not diminish the beneficial effects of exercise on muscle performance. While there is a potential for the sirolimus (rapamycin) group to exhibit a trend towards superiority in terms of exercise improvement, it is important to note that this study is not powered to conclusively determine superiority. Instead, our goal is to affirm that intermittent dosing of rapamycin alongside a regular exercise program will at least maintain, if not enhance, the muscle performance improvements that are typically observed with exercise alone in this demographic. This approach will provide valuable insights into the feasibility of incorporating rapamycin into exercise regimens for older adults, setting the stage for future studies that may be designed to explore the superiority of this combined intervention.

The rationale behind choosing the 30CST as our primary outcome measure lies in its relevance and sensitivity in assessing the functional muscle performance in older adults. By initiating an exercise regimen in participants who have not been regularly exercising—specifically, those not engaging in exercise that elevates heart rate for more than 15 min, three times a week—we anticipate observable improvements in muscle performance in the placebo group. This baseline improvement provides a critical comparative framework to evaluate the effects of rapamycin on exercise-induced muscle performance enhancements.

When measuring muscle performance, it is important to first define muscle strength, muscle power, and muscle endurance. Muscle strength refers to the amount of force a muscle can produce with a single maximal effort. Muscle power concerns work rate (work done per unit time) and is defined by the ability to exert a maximal force in as short a time as possible, as in accelerating, jumping, and throwing implements. Muscle endurance is the ability of muscles to exert force against resistance over a sustained period of time [30].

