**Table Tabd:** 

Age group	Mean	Standard deviation
60–69	14.0	2.4
70–79	12.9	3.0
80–89	11.9	3.6

We also have data on the change in the 30CST after exercise. A study of 20 healthy women aged between 65 and 79 demonstrated that after 12 weeks of a combined exercise intervention program with extra emphasis on balance and muscle strength found that the 30CST increased by 13.5% (14.8 ± 4 to 16.8 ± 3.4) [32]. A subsequent trial of 29 older adults included both males and females with an average age of 76 demonstrated a 20% improvement in the 30CST after a 12-week training program [33].

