### Statistical methods

#### Statistical methods for primary and secondary outcomes {20a}

As some of the feasibility issues are related to the efficacy analyses, they are described first. The efficacy analysis plan is intended to match the analysis plan of the full trial closely.

Efficacy analysisAnalysis sets◦ Intention-to-treat (ITT) analysis set: This set will be used for the primary analysis and will include all randomized participants in their originally assigned groups.◦ Per-protocol (PP) analysis set: this set will be used for sensitivity analyses and will include participants who complete at least 75% of the exercise sessions and take at least 75% of the protocol-stipulated doses of sirolimus (rapamycin) or placebo.General inferential analysis plan◦ Outcomes at 13 weeks will be analyzed using regression models, adjusting for baseline values of the outcomes. Generalized linear models (GLM) will be employed, selected during a blind review of the data without knowledge of group allocation.◦ Final analyses will utilize the selected GLMs, and parametric assumptions will be addressed using the wild bootstrap method to estimate standard errors [35, 36]. For larger trials, standard sandwich estimators of the variance would be used in lieu of the bootstrap.Handling missing data◦ Multiple imputations will be used to create 15 completed datasets. The nominal significance level for this phase 2a study will be set at 0.1; however, in line with current thinking regarding preliminary studies, the results will deemphasize testing and emphasize point and interval estimation, producing confidence intervals for active arm effect having between 75% and 95% confidence levels in increments of 5 percentage points [27].Sensitivity analyses◦ Sensitivity analyses will be performed on the per-protocol analysis set and the complete-data-only set, excluding cases with missing data.

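### The protocol promises to affirm that sirolimus does not diminish the exercise gain on the 30CST, but with no margin, no primary interval and 20 per arm it can only estimate the difference

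*Protocol article*

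**What the plan says.** Three places in the protocol article state the aim as showing no loss.

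- Objectives {7}, Primary objective: the study seeks to *establish* that adding sirolimus does not adversely affect the exercise-induced improvement.
- Trial design {8}: the primary objective, also labelled exploratory, is to "evaluate whether this combined intervention is at least equivalent to regular exercise alone in enhancing muscle performance in older adults".
- Outcomes {12}, Primary outcome: "our goal is to affirm that intermittent dosing of rapamycin alongside a regular exercise program will at least maintain, if not enhance" the gains usually seen with exercise. The same paragraph says the study is not powered to determine superiority conclusively.

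The design and analysis sections are built differently.

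- Sample size {14} says "arm sizes of 20, assuming no withdrawals, will provide 80% and 90% power, respectively, to detect fairly large" standardised differences: "effect sizes of 0.8 and 0.9, respectively, at a nominal significance level of 0.1". It also says the study is not confirmatory and that the number was set mainly by logistics.
- Sample size {14} prefers a total of 40 because "a 95% confidence interval for the variance will then have expected half-width of less than half the true variance".
- Statistical methods {20a}: "The nominal significance level for this phase 2a study will be set at 0.1". Testing is to be de-emphasised in favour of estimation, "producing confidence intervals for active arm effect having between 75% and 95% confidence levels in increments of 5 percentage points". That is five levels, none of them designated as primary.
- The only non-inferiority test in {20a} concerns the relatedness of adverse events. Its details are deferred to the final analysis plan. No corresponding statement is made for the 30CST.

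**The concern.** A no-loss claim needs a stated loss that would matter and an interval that excludes it. Power to detect a large difference gives neither: a study can fail to find a difference simply because it is small. Here the objective and the design address different hypotheses within one document, so this is not a detail left to an analysis plan that is not shown.

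At stake is the headline sentence of the results paper. Under the present objective, a null result from 40 people could be reported as affirming that weekly sirolimus leaves the exercise benefit intact. Nothing in the plan says which lower limit, at which confidence level, would justify or rule out that sentence.

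**Working it through.** **Inputs from the protocol article.** 20 per arm, allocation 1:1, level 0.1 (sidedness not stated). The 30CST SDs by age group are 2.4, 3.0 and 3.6, with means 14.0, 12.9 and 11.9 (Outcomes {12}, table). One cited exercise study moved from "14.8 ± 4 to 16.8 ± 3.4", a gain of 2.0 stands. A second reported a 20% improvement.

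**1. Reproducing the stated power.** Two-sample t-test, noncentrality d·√(20/2), 38 df, two-sided 0.1:

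| d | Stated | Noncentral t | Normal approximation |
|---|---|---|---|
| 0.8 | 80% | 79.9% | 81.2% |
| 0.9 | 90% | 87.5% | 88.5% |

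The 80% figure reproduces. The second is slightly optimistic: 90% needs d = 0.94 by t (0.925 by the normal approximation), and both round to 0.9. One-sided 0.1 would give 88.9% and 93.7%, so two-sided 0.1 is the reading that fits.

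**2. What the powered difference means in stands.** 0.8 × 2.4 = 1.9 and 0.8 × 3.6 = 2.9.

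**3. Cited exercise gain.** 16.8 − 14.8 = 2.0 stands. Applying 20% to the age-group means: 0.20 × 11.9 = 2.4 and 0.20 × 14.0 = 2.8. The powered difference is therefore about as large as the whole gain to be protected.

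**4. Interval width, unadjusted.** Half-width = t(38 df) × SD × √(2/20). For 90%, 1.686 × 0.316 = 0.533 SD; for 95%, 2.024 × 0.316 = 0.640 SD; for 75%, 1.168 × 0.316 = 0.369 SD.

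| SD | 75% | 90% | 95% |
|---|---|---|---|
| 2.4 | 0.9 | 1.3 | 1.5 |
| 3.0 | 1.1 | 1.6 | 1.9 |
| 3.6 | 1.3 | 1.9 | 2.3 |

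The verdict on no loss could change with the level chosen, since the 75% and 95% half-widths differ by 0.8 stand at SD 3.0.

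**5. Illustration: a true loss of 1.0 stand.** The 1.0 is chosen only for illustration. At SD 3.0, the two-sided 0.1 test is non-significant 72.5% of the time. With an assumed baseline correlation of 0.7, the residual SD is 3.0 × √(1 − 0.49) = 2.14 and the figure is 58%.

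**6. Illustration: excluding a 1.0-stand loss when there is none.** One-sided 0.05, 20 per arm: power is 36%, 27% and 22% at SD 2.4, 3.0 and 3.6 unadjusted, and 57%, 42% and 33% at correlation 0.7. For 80% power unadjusted, the margin would have to be 0.80 SD.

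**7. Variance precision.** Expected half-width over true variance = ½(df/χ²₀.₀₂₅ − df/χ²₀.₉₇₅).

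- 38 df: ½(38/22.88 − 38/56.90) = 0.497
- 37 df: ½(37/22.11 − 37/55.67) = 0.505
- 33 df: ½(33/19.05 − 33/50.73) = 0.541

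The statement holds for a pooled two-arm variance at 40. The residual variance that {20a} sets out to estimate, from a baseline-adjusted model, has 37 df, and losing four participants leaves 33.

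**The case against.** The strongest defence is that the document tempers its own aim. It calls the study a feasibility study, not confirmatory. It labels the primary objective exploratory, says larger studies are needed, and plans to emphasise intervals over tests. This defends the choice of 40, which is not disputed here, and it lowers the severity. It does not defend *establish*, *affirm* and *at least equivalent*, which promise a conclusion that the estimation plan cannot deliver without a margin.

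Four stronger readings are tempting, and the documents do not support them.

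- **That a non-significant test will be taken as proof of no loss.** No section states such a rule, and {20a} plays testing down. The gap is that no rule is given.
- **That the narrowest interval will be selected.** The plan commits to producing the whole series, so the 95% interval will also be seen. What is missing is the one that governs the conclusion.
- **That the planning figures are wrong.** The 90% is consistent with d = 0.94 rounded to 0.9. The planned baseline adjustment restores 90% at d = 0.9 (in raw SD units) with a correlation of only 0.3, which is an assumption: 0.9/√(1 − 0.09) = 0.943. The variance statement holds at 38 df and misses by 0.005 at 37. The no-withdrawal assumption behind the power figures is stated openly.
- **That 2.0 stands is the protocol's planning value.** It comes from one cited study of 20 women. The other cited study implies a larger gain, so shares of the gain must be shown as a range.

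**Conclusion.** The mismatch holds and is moderate. The article states a no-loss conclusion as its goal, powers only for a difference of 0.8 to 0.9 SD, gives no 30CST margin and ranks none of its five intervals. The unadjusted 90% half-width of about 1.3 to 1.9 stands, set against cited gains of 2.0 to 2.8 stands, means that even an observed difference of zero would leave a loss of a substantial part of the exercise benefit inside the interval: from 1.3/2.8 = 46% to 1.9/2.0 = 95% of it.

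This rests on the article's age-group SDs, complete follow-up and no covariate adjustment. Adjustment would narrow the interval, but the document gives no baseline correlation. The SDs in the cited exercise study (3.4 to 4) would put the half-width at 1.8 to 2.1 stands. The remarks on the power and variance figures are minor, and the conclusion does not depend on them.

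**What to change.** 1. In Objectives {7}, Trial design {8} and Outcomes {12}, restate the primary objective as estimating the between-arm difference in the 30CST at 13 weeks. Replace *establish*, *affirm* and *at least equivalent*.
2. In Statistical methods {20a}, name one interval as primary, for example the two-sided 90% interval, which matches the 0.1 level. Keep the others as supplementary. State that a non-significant difference is not evidence of no loss.
3. If a no-loss claim is to be kept, prespecify a margin in stands with its justification, judge it only on the lower limit of the primary interval, and report the power 40 participants give.
4. Minor, in Sample size {14}: say that the level is two-sided; give power at d = 0.9 as about 87.5% by an unadjusted t-test (90% needs d of about 0.94); and describe the variance half-width as about half, with no reserve for withdrawals.

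The cost is wording only, with no extra participants or visits. The downside is a less favourable claim: the trial could report how large a loss remains compatible with its data, but not that there is none.

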### Recruitment {15}

Participants will be recruited through advertisements approved by the Health and Disability Ethics Committee (HDEC), including newspaper flyers, social media, radio, and television.

## Assignment of interventions: allocation

### Sequence generation {16a}

Randomization will be carried out using block randomization with stratification for age. The algorithm producing the schedule will be coded using an R script by the trial statistician, who will keep the blocking scheme secret. The code will be seeded with a randomly generated number and run by the statistician and transmitted to a third party. The resulting schedule will consist of a password-protected Excel spreadsheet containing participant study identifiers and corresponding allocation arms.

### Concealment mechanism {16b}

The third party will transmit the password-protected Excel schedule to the pharmacy service (CompoundLabs), which will prepare the placebo and sirolimus (rapamycin) blister packs accordingly and identify them with study identifiers. These identifiers will be assigned to participants sequentially in order of recruitment. Concealment is by remote randomization and sending the signal directly to the pharmacy.

### Implementation {16c}

The trial statistician will generate the allocation sequence. Study coordinators at the clinical trial site will enroll participants. Once enrolled, participants will be assigned to interventions by the pharmacy service (CompoundLabs) based on the allocation sequence provided. The study coordinators and participants will remain blinded to the group assignments throughout the study.

## Assignment of interventions: blinding

### Who will be blinded {17a}

The study participants, care providers, outcome assessors, and data analysts will be blinded to the treatment groups. The trial statistician and CompoundLabs, who are not involved in the study activities at the site, will perform the randomization and code the blister packs of the drugs according to the allocation sequence.

Both sirolimus (rapamycin) and placebo capsules will be identical in appearance, taste, and packaging. CompoundLabs will allocate the active product capsules or placebo capsules into the blister packs with unique codes.

Adverse events will be reported and managed by blinded staff to ensure that the blinding is not compromised. Measures will be taken to maintain blinding throughout the study, including the use of a separate team for data analysis that is not involved in participant care or outcome assessment.

### Procedure for unblinding if needed {17b}

Unblinding is permissible under specific circumstances where knowledge of the participant’s allocated intervention is essential for their safety and well-being. This may include serious adverse events where the clinical management of the participant requires knowledge of the treatment assignment.

In such cases, the following procedure will be followed:Initiation of unblinding request: the treating physician or investigator will determine the necessity of unblinding and initiate the request. The request must be justified and documented, explaining the medical need for unblinding.Consultation with the principal investigator: the principal investigator will review the request. If unblinding is deemed necessary, the principal investigator will proceed with the unblinding process.Unblinding process: the principal investigator will contact the designated third party (CompoundLabs) responsible for maintaining the randomization code. CompoundLabs will provide the treatment allocation information directly to the principal investigator.Documentation: the unblinding event, including the reason for unblinding, the date, and the personnel involved, will be documented in the participant’s case report form and study records.Participant withdrawal: once unblinded, the participant will be withdrawn from the study to maintain the integrity of the trial. The participant will continue to receive appropriate medical care as required.Notification: the relevant ethics committee will be notified of the unblinding event and provided with the necessary documentation.

By following this procedure, we ensure that unblinding is conducted ethically and only when absolutely necessary to protect the participant’s health and safety.

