## Criteria for discontinuing or modifying allocated interventions {11b}

Participants have the right to withdraw from the study at any time without providing a reason. However, the site should try to ascertain a reason when possible. The principal investigator or a study site team member can be notified by email, phone call, or in person. Participants may be withdrawn from the study at the investigator’s discretion if it is in the participants' best interests or due to significant participant non-compliance.

Discontinuation of treatment based on adverse events are to be discussed with the principal investigator. Discovery of treatment allocation will unblind the participant and the principal investigator and will lead to early withdrawal of the participant from the study.

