## Plans to promote participant retention and complete follow-up {18b}

To ensure high participant retention and complete follow-up, several strategies will be implemented throughout the study:Regular communication◦ Weekly contact will be maintained with all participants through phone calls, texts, or emails to discuss compliance with the exercise and medication regimen, address any concerns, and document adverse events. Each contact attempt will be documented in the participant’s source documents.Convenience and support◦ Exercycles will be delivered and installed at participants’ homes by Rutherford Fitness, ensuring they have the necessary equipment to complete the exercise program.◦ Participants will receive detailed instructions and support for using the exercycle and completing the exercise regimen.Monitoring and feedback◦ Participants will be monitored regularly for adherence to the study protocol. Weekly phone calls will include discussions about compliance, and any issues will be addressed promptly.◦ Participants will be encouraged to complete their daily diaries to record exercise activities, medication administration, and any adverse events. Compliance will be reviewed during the interim visit, and retraining will be provided as necessary.Adverse event management◦ Adverse events will be closely monitored and managed by blinded staff to ensure that participants’ safety is prioritized without compromising the blinding of the study.◦ Participants experiencing significant adverse events will be consulted with the principal investigator to determine the best course of action, including the possibility of unblinding if necessary for safety reasons.Data collection for withdrawn participants◦ Efforts will be made to collect outcome data for participants who discontinue or deviate from the intervention protocols. This includes attempting to conduct end-of-treatment (EOT) assessments for those who withdraw early from the study.◦ Participants who withdraw will be asked to return all study materials, including exercycles and study medication, and complete final assessments if they agree.Participant engagement◦ Regular updates on the study’s progress and findings (where appropriate) will be shared with participants to keep them engaged and informed about the importance of their contribution.

By implementing these strategies, the study aims to maintain high retention rates and ensure complete and accurate follow-up data.

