### Methods in analysis to handle protocol non-adherence and any statistical methods to handle missing data {20c}

Definition of analysis populationsIntention-to-treat (ITT) analysis set: this set will be used for the primary analysis and includes all randomized participants analyzed according to their original assigned groups, regardless of protocol adherence.Per-protocol (PP) analysis set: this set will be used for sensitivity analyses and includes participants who complete at least 75% of the exercise sessions and take at least 75% of the protocol-stipulated doses of sirolimus (rapamycin) or placebo.

Handling protocol non-adherenceThe primary analysis will follow the ITT principle, which means all participants will be analyzed as randomized. This approach maintains the benefits of randomization by including all participants, regardless of adherence, and is appropriate for estimating the effect of treatment in a real-world setting.Sensitivity analyses using the PP set will help to understand the effect of the intervention among those who adhered to the protocol. This analysis will exclude participants who fail to meet the adherence criteria, providing insights into the efficacy of the intervention when administered as intended.

Statistical methods to handle missing dataMultiple imputation: missing data will be handled using multiple imputations, which helps to provide unbiased estimates by incorporating the uncertainty associated with missing data.Complete-case analysis: a complete-case analysis will be conducted, including only participants with no missing data, to compare and validate the results obtained from the multiple imputation method.Sensitivity analyses: sensitivity analyses will be conducted to assess the impact of different assumptions about the missing data. This may include:◦ Exploring the pattern and impact of missing data on the primary and secondary outcomes.◦ Comparing results from different imputation models to ensure robustness.

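### Mandatory withdrawal from the study after unblinding, and discretionary withdrawal for non-compliance, can cost the intention-to-treat analysis week-13 outcomes that it needs

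*Protocol article*

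**What the plan says.** Two sections of the protocol article end study participation after unblinding:

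- Procedure for unblinding {17b}: "once unblinded, the participant will be withdrawn from the study to maintain the integrity of the trial". The stated trigger is a safety need. On the circumstances, it says: "This may include serious adverse events where the clinical management of the participant requires knowledge of the treatment assignment".
- Criteria for discontinuing or modifying allocated interventions {11b}: "Discovery of treatment allocation will unblind the participant and the principal investigator and will lead to early withdrawal of the participant from the study".

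Both are mandatory. Section {11b} also lets the investigator withdraw a participant "due to significant participant non-compliance", or in the participant's best interests. That part is discretionary.

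The analysis sections take a different line. Section {20c} defines the primary set as "all randomized participants analyzed according to their original assigned groups, regardless of protocol adherence", and section {20a} analyses outcomes at 13 weeks with baseline adjustment, using 15 multiply imputed datasets.

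The bridge between the two is section {18b} on retention. It promises an effort to gather outcomes from people who stop or depart from the intervention, which includes "attempting to conduct end-of-treatment (EOT) assessments for those who withdraw early from the study", subject to their agreement. It does not say when that assessment takes place.

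**The concern.** An analysis that ignores adherence needs outcomes from people who did not adhere or whose treatment was disclosed. The conduct rules allow or require those same people to leave the study. An analysis plan cannot cure this later, because the rule decides which data exist.

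The reasons for leaving are not neutral. Unblinding follows a safety event, and non-compliance can follow poor tolerance or failing function. Either can be related to the week-13 30-Second Chair-Stand Test (30CST), and either could occur more often in one arm. The trial hopes to show that sirolimus does not reduce the gains from exercise. If poor outcomes were lost mainly from the sirolimus arm, the error would favour that conclusion; if mainly from placebo, it would run the other way.

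**Working it through.** **1. Is a week-13 value secured for a withdrawn participant?**

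| Section | Effect |
|---|---|
| {17b}, {11b} unblinding or discovery | Leaves the study; mandatory |
| {11b} significant non-compliance | May leave the study; investigator's choice |
| {20a}, {20c} | Week-13 outcome analysed for all randomised |
| {13} schedule | Final visit at Day 91 (+7), with no provision for withdrawn participants |
| {18b} | Attempted collection, by agreement, timing unstated |

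No section commits to a Day 91 assessment once someone has been withdrawn. An assessment made near the time of withdrawal would not be the week-13 outcome.

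**2. The plan's own figure.** Sample size {14} assumes 20 per arm, no withdrawals and a significance level of 0.1, and gives 80% power for d = 0.8 and 90% for d = 0.9. Sidedness is not stated. With a two-sided test and the normal approximation, power ≈ Φ(d√(n/2) − 1.645):

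- d = 0.8: Φ(2.530 − 1.645) = 81.2%
- d = 0.9: Φ(2.846 − 1.645) = 88.5%

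Both are within 2 points of the stated values. The noncentral t gives 79.9% and 87.5%.

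**3. Power after losses from one arm** (two-sided t; the losses are assumed, as the document gives no withdrawal rate):

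| Arm sizes | d = 0.8 | d = 0.9 |
|---|---|---|
| 20 v 20 | 79.9% | 87.5% |
| 19 v 20 | 79.0% | 86.7% |
| 17 v 20 | 76.8% | 84.9% |

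Precision is a minor matter.

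**4. Bias.** Suppose k of 20 in one arm are withdrawn and their true week-13 mean lies Δ below what is imputed.

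- Arm mean with imputation: [(20 − k)m + k·i]/20, where m is the observed mean and i the imputed mean
- True arm mean: [(20 − k)m + k(i − Δ)]/20
- Overstatement: kΔ/20

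Take Δ = 2.0 stands, meaning the whole expected gain is missed. This is the rise from 14.8 to 16.8 in the 12-week exercise study of 20 women cited under Primary outcome {12}.

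| k (assumed) | Overstatement | Share of the 2.0-stand gain |
|---|---|---|
| 1 | 1/20 × 2.0 = 0.10 | 5% |
| 2 | 2/20 × 2.0 = 0.20 | 10% |
| 3 | 3/20 × 2.0 = 0.30 | 15% |

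With Δ = 1.0 the values halve, to 0.05 to 0.15 stands. Against the normative standard deviations of 2.4 to 3.6 in the same section, 0.10 to 0.30 stands is 0.10/3.6 = 0.03 to 0.30/2.4 = 0.13 SD. The difference between arms shifts by the same amount if the other arm has no such losses; similar losses in both arms would largely cancel.

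**The case against.** The opposing case has real substance.

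- **Intention to treat.** A reader might infer that the rules contradict the primary analysis. They do not: withdrawn participants stay in their randomised arm, with missing values imputed. The damage is to the data that the analysis relies on.
- **Non-compliance.** A reader might infer that non-compliant participants are always withdrawn. Section {11b} only permits it, for significant non-compliance. The per-protocol set, the adherence subgroups {20b} and the instrumental-variable analysis {20a} all presuppose that some non-adherers remain and provide outcomes.
- **Retention effort.** Section {18b} promises more than a single assessment on leaving. It states a general effort to collect outcomes, and that the assessment happens at the moment of withdrawal would be an inference.
- **Imputation.** The model is not stated, so it cannot be said that values will be drawn only from compliant completers. A week-6 30CST will exist for anyone withdrawn after that visit, and {20c} plans sensitivity analyses under other missing-data assumptions.
- **Safety.** It would be too strong to say that safety follow-up stops. Section {22} follows serious events until they resolve or stabilise, and {17b} continues medical care. What is unclear is whether new events are collected after withdrawal.
- **Direction and size.** No figure in the document shows that these withdrawals will be commoner on sirolimus. Unblinding is meant to be rare, and the trial is a feasibility study that puts estimation ahead of testing.

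These points limit the claim but do not remove it. The unblinding rule remains mandatory, no week-13 assessment is secured, and sensitivity analyses only explore a gap that continued follow-up would prevent.

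**Conclusion.** The concern holds in limited form. Withdrawal from the study is required after unblinding or discovery of allocation, and permitted for significant non-compliance, while the primary analysis wants week-13 outcomes irrespective of adherence. Followed as written, the rules create avoidable missing outcomes for reasons linked to safety or adherence, which may differ by arm. Imputation under missing at random would not correct this.

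The likely size is modest: 0.10 to 0.30 stands in one arm's mean. That rests on three assumptions: 1 to 3 of 20 withdrawn, a shortfall of 2.0 stands each against the imputed value, and an imputation that does not capture the shortfall. The number affected cannot be derived from the document and could be zero. The correction is worth making because it is cheap and acts before data are lost, not because a large bias has been shown.

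**What to change.** Reconcile {11b} and {17b} with {18b}, {20a} and {20c} by separating two events: stopping study product and stopping follow-up.

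- State that unblinding, discovery of allocation or non-compliance does not by itself end follow-up.
- Keep the Day 91 assessments (30CST, grip strength, 6-minute walk, SF-36, bloods) and adverse event collection, with outcomes measured by assessors who remain blinded and analysed in the randomised arm.
- Allow two exits: the participant withdraws consent, or the investigator judges that assessment is not in the participant's best interests.
- State in {18b} when the end-of-treatment assessment takes place. Use any earlier value as an auxiliary variable in the imputation model, not as the week-13 outcome.

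Whether study product stops is a clinical decision outside this change.

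The cost is protocol wording and an instruction to the site. The Day 91 visit is already in the schedule; the document does not say how it is funded. One small downside is that a few participants will know their arm at an effort-dependent final test. They can be flagged, and a sensitivity analysis can show whether they matter.
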